#### Quantitative Measures: Additional Constructs

We will additionally assess 3 quantitative measures: (1) supervisory practices, (2) clinician social desirability, and (3) the cost of Tele-BE. Clinician-reported CBT-specific supervisory practices will be measured at weeks 1 and 12 to identify potential differences between conditions. We adapted the Self-Reported Therapist Intervention Fidelity for Youth Supervision, originally a supervisor-report measure of supervisory practices, to be inclusive of clinicians working with adult clients and to specifically capture supervision related to CBT structural components. The adapted supervisory measure consists of 14 items rated on a 7-point scale, indicating the extent to which specific supervisory techniques are used (1=not at all to 7=extensively). Additionally, the 17-item Edwards Social Desirability Scale will be included in the baseline clinician survey as a potential covariate for clinician-reported engagement with the Tele-BE platform [71]. Finally, we will track the following cost metrics to inform more formal cost evaluations in future studies: (1) anticipated annual cost per clinician user for Tele-BE, including variation based on the number of patients with whom the platform is used—these estimates will be calculated in collaboration with our web development team to account for both base subscription costs and ongoing web maintenance;; (2) time required to train clinicians to use Tele-BE, which we expect to be minimal, tracked for each clinician and averaged at study completion; and (3) time clinicians spend logged into the Tele-BE interface, captured via web analytics.

#### Qualitative: Clinician Interviews (Aims 3 and 4)

All clinicians, regardless of condition, will complete interviews after their patients finish the trial period. The first portion of the interview will be identical for all clinicians and will explore perceptions of their intentions and the determinants of intentions to use CBT structural components throughout the trial. This portion addresses aim 3 questions regarding engagement of target mechanisms. Questions will be adapted from an established theory-guided qualitative interview [72], which includes items on attitudes toward an EBP, self-efficacy, perceived norms, and motivation. Questions will be asked separately for each structural CBT component of interest (Table 1). All clinicians will also be asked about barriers they encountered during the trial in using structural components, with specific probes regarding the impact of cognitive burden on delivery (eg, “To what extent, if at all, did factors like forgetting due to competing demands make it easier or harder for you to set an agenda?”). Collecting these responses from all clinicians will allow us to examine themes by condition to determine whether Tele-BE better engaged target mechanisms and reduced barriers to structural component delivery. The second portion of the interview will be administered only to clinicians randomized to Tele-BE and will address aim 4 by querying acceptability and any feasibility issues that arose. Patient interview questions may include, “How was your experience with Tele-BE? What aspects were easy or difficult to use?” We will also use self-reported fidelity data collected via web analytics to ask clinicians specific questions about how they decided to act on or override Tele-BE nudges (eg, electing not to review a planned homework) and their rationale for doing so. Clinicians will also be asked about any ethical concerns they or their patients might have, such as undue pressure to deliver structural CBT components or potential negative impacts on treatment processes. Finally, clinicians will be queried about any unanticipated resources required to engage with Tele-BE and asked to estimate how the platform influenced the time needed to prepare for or document a therapy session, informing our cost estimates.

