### Aims 3 and 4: Evaluate the Preliminary Effectiveness of Tele-BE in Engaging Target Mechanisms and Enhancing Clinician Fidelity to CBT

#### Overview

Although aims 3 and 4 are scientifically distinct, study procedures will occur concurrently and are described together. We will randomize 30 clinicians who already provide individual CBT via telehealth for at least 2 clients to either Tele-BE or telehealth as usual (Tele-AU), with 15 clinicians per condition. Allocation will be balanced within organizations to ensure equal representation across conditions within each agency. Each participating clinician will deliver treatment to 2 patients over 12 weeks, the standard length for many CBT protocols, and clinician fidelity to CBT structural components will be tracked in each condition. While the primary goal is to evaluate the feasibility of our design and measurement approach for a fully powered trial, we will also measure patient symptoms, therapeutic alliance, and patient-centered care to explore preliminary clinical effectiveness outcomes and assess any potential concerns with Tele-BE (eg, clinician distraction or impact on therapeutic alliance) using mixed methods.

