#### Quantitative Measures: Aim 4 Primary Outcomes

Primary outcomes for aim 4 include Tele-BE acceptability, feasibility, and any potential ethical concerns raised by clinicians or patients regarding the platform. Acceptability will be assessed using the AIM [52]. Feasibility will be examined through a combination of the FIM [52] and web analytics data. Tele-BE usability will be evaluated using the SUS [53]. Psychometric support for these measures has been described above under aim 1 activities. All measures will be administered to clinicians in both conditions to allow comparison of quantitative scores for acceptability and feasibility. These measures will be supplemented with clinician and patient interviews, which will also assess potential ethical concerns, including any pressure clinicians may have felt from the platform to deviate from care they believed was in the best interest of their patients.

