#### Qualitative: Patient Interviews (Aim 4)

We will randomly select 1 patient per therapist to participate in a qualitative interview at the end of the 12-week trial period. If a patient declines, the second patient per therapist will be selected, ensuring 1 patient per therapist completes an interview. In the first half of each interview, research staff will ask patients about their perceptions of the therapeutic relationship during the trial (including any changes from before the trial), satisfaction with services received over the preceding 12 weeks, and perceived effectiveness of psychosocial treatment. This will allow comparison by condition to examine whether themes related to treatment processes differ depending on whether the clinician used Tele-BE or Tele-AU. In the second half of the interview, staff will query patients about their awareness of and perceptions regarding Tele-BE or Tele-AU and its influence on clinician behavior. Staff will then provide patients with information about Tele-BE and ask about their perceived likes and dislikes regarding their clinician’s use of an enhanced telehealth interface to deliver care.

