#### Missing Data Considerations

Based on ongoing prospective community mental health studies with comparable follow-up periods [73], we anticipate a clinician dropout rate of approximately 20% over 12 weeks, with minimal patient dropout among retained clinicians since patients are drawn from established caseloads. The mixed effects models described above will provide valid estimates and standard errors under the assumption that dropout is ignorable (ie, dependent only on observed outcomes and participant characteristics). We will conduct additional analyses to assess the sensitivity of our results to this ignorability assumption. Given the study’s sample size, our primary focus will be on overall completion of the 12-week protocol. We will use logistic regression models to examine whether prior outcomes or baseline variables are individually associated with study completion. Variables showing strong associations with completion will be combined into a multiple logistic regression model to predict completion. Based on participant-level dropout probabilities estimated from this model, we will perform exploratory inverse probability–weighted versions of the main mixed effects models and compare intervention effect estimates from the weighted and unweighted models.

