#### Progression Criteria

We will examine acceptability and feasibility data, as well as trends in observed fidelity, to determine whether the pilot trial results support progression to a larger, confirmatory trial. For acceptability and feasibility, we will descriptively compare mean AIM and FIM scores between Tele-BE and Tele-AU clinicians; comparable scores would support the utility of progressing. If Tele-BE scores are notably lower than those in the Tele-AU condition, this would raise concerns regarding its acceptability and feasibility. Regarding fidelity, we will look for trends indicating (1) greater use of structural components in the Tele-BE condition relative to Tele-AU as measured by the CTRS, or (2) increased motivation to use CBT structural components in Tele-BE relative to Tele-AU, as suggested by qualitative analysis.

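### Aim 4 interviews are timed to the end of the trial and no contact at withdrawal is stated, so about 3 of 15 Tele-BE clinicians may be missing from the ethics and acceptability interviews

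*Protocol article*

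**What the plan says.** All references are to the protocol article.

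- **Outcome.** The article defines it as follows: "Primary outcomes for aim 4 include Tele-BE acceptability, feasibility, and any potential ethical concerns raised by clinicians or patients regarding the platform" (section Quantitative Measures: Aim 4 Primary Outcomes). No scale is named for ethical concerns; that section assigns them to the clinician and patient interviews.
- **Clinician interview.** Qualitative: Clinician Interviews (Aims 3 and 4): "All clinicians, regardless of condition, will complete interviews after their patients finish the trial period". The part that serves Aim 4 is restricted by arm: "The second portion of the interview will be administered only to clinicians randomized to Tele-BE and will address aim 4".
- **Patient interview.** Qualitative: Patient Interviews (Aim 4): one randomly chosen patient per clinician will "participate in a qualitative interview at the end of the 12-week trial period". A substitute is provided for a patient who declines. Nothing is said about patients whose clinician has left.
- **Dropout.** Missing Data Considerations: "we anticipate a clinician dropout rate of approximately 20% over 12 weeks, with minimal patient dropout among retained clinicians". The inverse-probability weighting there applies to the main mixed effects models.
- **Ratings.** Table 2 schedules AIM, FIM and SUS at weeks 1, 5, 9 and Post.
- **Progression.** Progression Criteria: "we will descriptively compare mean AIM and FIM scores between Tele-BE and Tele-AU clinicians". No time point, analysis set or rule for missing ratings is given. On fidelity, the section accepts either a CTRS trend or a qualitative sign of greater motivation to use the components.

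**The concern.** Aim 4 asks whether clinicians and patients find the platform acceptable and whether its nudges create undue pressure. A clinician who finds it intrusive may stop using it, or leave the study. For that clinician the stated interview trigger, patients finishing the trial period, may never be met. The same applies to the interviewed patient.

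The loss need not be equal between arms. Tele-AU clinicians keep their organization's usual telehealth methods, so dislike of Tele-BE cannot be their reason for leaving. In Tele-BE it can. The people most likely to report pressure or burden are then the least likely to be asked.

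Two uses of the data are exposed: the ethical-concerns outcome, which rests mainly on the interviews, and the progression decision, which draws on AIM/FIM means and on interview evidence about motivation. A later analysis plan can choose how to handle missing ratings, but it cannot recover an interview that was never held.

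**Working it through.** The article gives no expected number of interviews, so there is no such figure to reproduce. Its own counts agree: 30 × 2 = 60 patients and 60 × 12 = 720 sessions.

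**Inputs from the article.** 30 clinicians, "with 15 clinicians per condition" (Overview); dropout of about 20% (Missing Data Considerations); one interviewed patient per clinician; the Aim 4 interview portion for Tele-BE clinicians only.

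**1. Number affected.**
- Leavers: 0.20 × 30 = 6, so 24 remain.
- Even split: 0.20 × 15 = 3 leavers per arm. If leavers are not interviewed, 12 of 15 Tele-BE clinicians answer the Aim 4 portion, and 3 patient interviews in that arm are also at risk.
- Range: 0 to 6 of the leavers could be in Tele-BE, leaving 15 to 9 of 15 interviewed.
- If leaving is unrelated to arm, the hypergeometric probability of a 3:3 split is 0.349. The chance of 4 or more in Tele-BE is 0.241 + 0.076 + 0.008, about 0.33.

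**2. Ethical concerns (rates assumed).** Suppose 10% of stayers and 50% of leavers hold a concern. Interviews with stayers alone show 10%. Over all 15:
- 3 leavers: (3 × 0.50 + 12 × 0.10)/15 = 18%.
- 6 leavers: (6 × 0.50 + 9 × 0.10)/15 = 26%.
- With 30% to 80% among leavers: 14% to 24% (3 leavers) or 18% to 38% (6 leavers).

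**3. Final AIM/FIM among completers (gap assumed).** Overstatement of the Tele-BE mean = share of leavers × gap between stayers and leavers.

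| Leavers in Tele-BE | Gap 0.5 SD | Gap 1.0 SD | Gap 1.5 SD |
|---|---|---|---|
| 3 of 15 | 0.10 SD | 0.20 SD | 0.30 SD |
| 6 of 15 | 0.20 SD | 0.40 SD | 0.60 SD |

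The standard error of the arm difference at 12 v 12 is √(1/12 + 1/12) = 0.41 SD. With 3 leavers, the bias is smaller than the sampling error across this range.

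**4. Ratings that leavers already have.** If dropout is uniform over 12 weeks (assumed), (12 − 5)/12 = 58% of leavers pass week 5 and (12 − 9)/12 = 25% pass week 9. About 30 − 6 × 5/12 = 27.5 clinicians are still present at week 5 and 30 − 6 × 9/12 = 25.5 at week 9. Many leavers therefore have a rating after some weeks of use. One who leaves at week 3 has only the baseline/week 1 rating.

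**The case against.** The strongest reply is that the interview sentence covers all clinicians and then only sets a time. The trial period is defined in calendar weeks (Design Considerations), so someone who stops at week 3 can still be approached at week 12. No section says that leavers are excluded, and stopping the platform is not the same as losing contact. A full protocol may also contain a withdrawal procedure that an article would omit.

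This stands in part: missing interviews are a risk, not a stated rule. It does not remove the point. The stated trigger does not fit a clinician whose patients never finish, and universal interviewing is hard to square with 20% dropout.

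The rest of the reply corrects stronger readings that a reader might infer:

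- **Leavers are absent from Aim 4 altogether.** They are not. Ratings from weeks 1, 5 and 9 before leaving are kept. Overrides are logged for each recorded Tele-BE session. Ethical Considerations commits to collecting concerns that participants raise, though a volunteered concern is not the same as a systematic question.
- **The AIM/FIM comparison uses only those who complete.** Progression Criteria does not say so; it is silent on time point and missing ratings.
- **All 6 patients of 3 leavers are lost to interview.** Only one per clinician is interviewed, so about 3.
- **The bias would reverse the progression decision.** Nothing shows this. The 20% comes from other community mental health studies and is not an estimate of exits caused by the platform. Every leaver score above is assumed, and recording and questionnaires burden both arms.

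**Conclusion.** The point holds for the interviews and for the final ratings. If dropout is as expected and leavers are not contacted, about 3 of 15 Tele-BE clinicians (0 to 6), and the one interviewed patient of each, would be missing from the main source on ethical concerns and from the qualitative progression evidence. They would also lack the last AIM, FIM and SUS.

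The loss may favor Tele-BE, because leaving on account of the platform is possible only there. Its size is unknown: the 10%-against-18% illustration and the 0.10 to 0.30 SD range for 3 leavers rest on assumed values. The loss of interviews is the stronger part, since it cannot be repaired in analysis. The effect on AIM/FIM means is secondary. The article does not support saying that leavers drop out of the acceptability answer as a whole. This is worth changing before Aim 3 recruitment, but it does not invalidate the design.

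**What to change.** **In the two interview sections and Table 2.** In both arms, offer the clinician interview and a last AIM, FIM and SUS at withdrawal, and offer the patient interview then too. Record whether the platform was a reason for leaving.

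**In Progression Criteria.** Name the time point of the AIM/FIM comparison. Include each randomized clinician's last available rating after first use, at least as a sensitivity display. Report platform-related withdrawals by arm beside the means. Scoring such withdrawals as not acceptable would be an analytic preference, and this point does not depend on it.

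**Cost.** Protocol wording, and earlier timing of assessments already planned, for about 6 clinicians. Some leavers will decline, and last ratings will come from different time points, so they should be shown with their timing.

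If a full protocol already provides for contact at withdrawal, the interview sections need only say so.

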#### Qualitative: Patient Interviews (Aim 4)

We will randomly select 1 patient per therapist to participate in a qualitative interview at the end of the 12-week trial period. If a patient declines, the second patient per therapist will be selected, ensuring 1 patient per therapist completes an interview. In the first half of each interview, research staff will ask patients about their perceptions of the therapeutic relationship during the trial (including any changes from before the trial), satisfaction with services received over the preceding 12 weeks, and perceived effectiveness of psychosocial treatment. This will allow comparison by condition to examine whether themes related to treatment processes differ depending on whether the clinician used Tele-BE or Tele-AU. In the second half of the interview, staff will query patients about their awareness of and perceptions regarding Tele-BE or Tele-AU and its influence on clinician behavior. Staff will then provide patients with information about Tele-BE and ask about their perceived likes and dislikes regarding their clinician’s use of an enhanced telehealth interface to deliver care.

#### Preliminary Analyses

Data screening and analysis of missing data will be conducted following best practices. We will evaluate the psychometric properties of all scales used to assess constructs of interest (eg, coefficient alpha) to confirm adequate performance. Baseline variables will be analyzed as a randomization check to ensure comparable characteristics between clinicians in the Tele-BE and Tele-AU groups. We will also assess the sensitivity of our main comparisons to medium-to-large effect size imbalances between the randomized groups.

#### Quantitative Analyses

Aim 3 primary analyses will focus on structural component scores from the CTRS generated via the Lyssn platform, dichotomized as present or absent. An aggregate fidelity metric will be calculated for each session by summing the number of components present. We will use a linear mixed effects regression model to estimate the trajectory of completion scores over the 12 weeks of treatment. Fixed effects will include linear and quadratic time trends to capture the overall trajectory, although more flexible specifications will be considered if needed. To account for correlations arising from patients nested within clinicians, a random intercept for clinicians will be included, along with correlated residuals to address within-patient correlations over time. The model will use data from all 12 sessions to estimate time trends, as well as session means and standard errors for each session. Additionally, monthly estimates will be generated to align with participant survey intervals. As described above, we will also create an overall structural component sum score for each session by summing the total structural components rated as “completed at or above the satisfactory threshold” on the CTRS. If sufficient variability exists, we will model the time course using mixed effects models as described previously. If the score range is too narrow, we will use mixed effects ordinal regression models, with fixed and random effects specified similarly. All analyses will include patient demographics (eg, age, diagnosis) as covariates. In addition to CTRS-based fidelity measures, self-reported fidelity will be captured for the intervention group using web analytics data. The primary self-report measure will parallel the CTRS, summing the number of structural components rated as present. We will use a bivariate-response mixed effects model, treating CTRS and web-based measures as concurrent responses across the 12 weeks, to compare overall levels and trends over time between the 2 measurement methods.

To examine secondary outcomes (intentions and determinants of intentions), we will model monthly trends in clinician-reported intentions, attitudes, self-efficacy, and perceived social norms using approaches analogous to those described for fidelity measures. The primary distinction is that time will be treated as a categorical variable, reflecting the 3 assessment points rather than the 12 weekly sessions.

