#### Quantitative Measures: Aim 3 Primary Outcomes

The primary outcome for aim 3 is clinician fidelity to structural components of CBT. We will code all recorded therapy sessions (up to 720 sessions: 60 patients × 12 sessions) for the presence of 6 structural components: (1) discussion or review of patient symptoms, (2) homework review, (3) agenda setting, (4) skill instruction or review, (5) skill practice, and (6) out-of-session practice (homework). Coding will use items from the CTRS, a gold-standard CBT fidelity measure with 11 observer-rated items, including those indexing the specific structural components of interest (homework review and planning, agenda setting, skill instruction, and skill practice) [60]. Each CTRS item is scored on a 7-point Likert scale ranging from 0 (poor) to 6 (excellent), allowing fidelity to be defined in 2 ways: (1) the presence or absence of each component, and (2) whether each component meets a competency threshold (ie, a score of 4 or higher). Our primary focus will be on the presence/absence of each component, calculated as the sum of the binary outcomes. Presence above the competency threshold will serve as a secondary outcome. The CTRS demonstrates strong internal consistency and interrater reliability [60], as well as strong interrater agreement for general competency [32]. Importantly, the CTRS includes a subscale assessing structural competency [31], in addition to scores for specific structural components and an overall competency score.

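### The primary fidelity model has no clinician-level slope and does not say which between-arm contrast is the Tele-BE effect, so its claim of valid standard errors is too broad for trend comparisons

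*Protocol article*

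**What the plan says.** Under Overview (aims 3 and 4), clinicians are randomised "to either Tele-BE or telehealth as usual (Tele-AU), with 15 clinicians per condition". "Each participating clinician will deliver treatment to 2 patients over 12 weeks", which gives "up to 720 sessions: 60 patients × 12 sessions". The primary outcome is a count from 0 to 6 per session: "Our primary focus will be on the presence/absence of each component, calculated as the sum of the binary outcomes".

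Under Quantitative Analyses, the model for that count is a linear mixed model. Its mean structure is given as: "Fixed effects will include linear and quadratic time trends to capture the overall trajectory, although more flexible specifications will be considered if needed". For the covariance, "a random intercept for clinicians will be included, along with correlated residuals to address within-patient correlations over time". Covariates are also named: "All analyses will include patient demographics (eg, age, diagnosis) as covariates". No arm term, arm-by-time term or clinician-level slope is written.

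Missing Data Considerations then states: "The mixed effects models described above will provide valid estimates and standard errors under the assumption that dropout is ignorable". The same section plans to compare the intervention's estimated effect between weighted and unweighted versions of these models. Preliminary Analyses also refers to main comparisons between the randomised groups. A between-arm contrast is therefore intended, but its form is never written.

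**The concern.** Treatment is assigned to clinicians. A difference between arms in trend over the 12 weeks has to be judged against how much clinicians differ from one another in trend. A random intercept lets clinicians differ in level only. Within-patient residuals are independent between a clinician's two patients, so they cannot carry a slope that those patients share. The allowance for more flexible specifications is attached to the fixed effects and does not supply a random slope.

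Variation in trend is plausible on the protocol's own account. The Introduction describes two kinds of clinician who need different support. Study Setting reports wide variation in intentions and training effects that fade over time. Table 1's badges and supervisor feedback respond to each clinician's own earlier behaviour.

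Once arm is added to the written mean structure, three arm parameters appear (level, linear, quadratic), and none is designated as the Tele-BE effect. The choice matters: a nudge that works from the first session shows as a level difference, not a slope. At stake are how far any reported trend difference can be trusted and what a later confirmatory trial is told to expect.

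**Working it through.** **No planned figure to reproduce.** The article states no alpha, power, effect size or SD. Its one count is right: 60 × 12 = 720.

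**Inputs from the protocol article.** K = 30 clinicians, 15 per arm, 2 patients each, 12 weekly sessions; about 20% clinician dropout, so 30 × 0.8 = 24.

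**Assumed, not in the documents.** Total session SD 1.2 components (variance 1.44); clinician share 0.25 (0.36), patient share 0.10 (0.144), remainder 0.936 with AR(1) correlation 0.3. The SD between clinicians in week 1 to 12 change, τ, runs from 0 to 1.2. The test is two-sided at a nominal 5% using 1.96.

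**Fitted model.** The planned structure (clinician intercept, AR(1) residuals within patient) plus arm × (intercept, linear, quadratic). Time is coded s = (week − 6.5)/11, so the linear coefficient is the week 1 to 12 change.

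**Formulas.** With K/2 clinicians per arm, the true variance of the arm difference in slope is (4/K)(v₀ + τ²), where v₀ is each clinician's slope variance from all other sources. The model's SE comes from fitting the planned covariance to the true one in large samples. The rejection rate under no effect is 2[1 − Φ(1.96 × model SE / true SE)].

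At K = 30 and τ = 0 the true SE is 0.283 (variance 0.0801). At τ = 0.8, add (4/30) × 0.64 = 0.0853, giving √0.1654 = 0.407. The model reports 0.326. The ratio is 0.80 and 1.96 × 0.80 = 1.57, so the rejection rate is 11.6%.

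| τ | True SE | Model SE | Ratio | Rejects |
|---|---|---|---|---|
| 0 | 0.283 | 0.307 | 1.08 | 3.4% |
| 0.3 | 0.303 | 0.309 | 1.02 | 4.6% |
| 0.5 | 0.337 | 0.314 | 0.93 | 6.7% |
| 0.8 | 0.407 | 0.326 | 0.80 | 11.6% |
| 1.2 | 0.522 | 0.350 | 0.67 | 18.9% |

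With 24 clinicians both SEs grow by √(30/24), so these large-sample rates do not change.

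**Averaged contrast.** Over weeks 1 to 12, s averages zero, and any shift in a clinician's mean is carried by the random intercept. Model and true SE are both about 0.258 at every τ, and the rejection rate is 5%.

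**Check by simulation under different variances.** REML fits, 600 runs per cell; clinician SD 0.8, residual SD 1.2, AR(1) 0.3; contrast is the arm difference in week 1 to 12 change.

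| Slope SD | 30 clinicians | 24 clinicians |
|---|---|---|
| 0 | 5.7% | 4.5% |
| 0.5 | 8.5% | 7.0% |
| 1.0 | 13.0% | 13.7% |
| 1.5 | 19.5% | 22.8% |

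- A t reference with K − 2 df does not cure it: 12.8% and 12.5% at slope SD 1.0.
- An unstructured within-patient residual reduces but does not remove it: 6.4%, 9.2% and 11.5% at slope SD 0.5, 1.0 and 1.5 (analytic).
- A clinician random slope with the t reference (500 runs per cell) gives 3.8% to 5.6% in every cell.
- The averaged contrast under the planned covariance does not move with slope SD: 6.0–6.2% (30) and 8.7–9.0% (24) with 1.96; 5.0% and 6.5–6.7% with t.

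**The case against.** The strongest reply is that this is a condensed article about a pilot. The main goal under Overview is feasibility of the design and measurement, no significance level is set, and Progression Criteria rests on descriptive trends and qualitative findings. That stands, and it limits the consequence: no stated decision rule turns an understated standard error into a false claim of effect.

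Three stronger readings are tempting but unsupported.

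- **That the plan contains no between-arm comparison.** Preliminary Analyses, Missing Data Considerations and Progression Criteria all presuppose one. It is unspecified, not absent.
- **That the standard errors are simply invalid.** With little slope variation the test is near nominal, and the averaged difference is unaffected. The documents do not say how much clinicians' slopes vary. The assumed between-clinician SD in level is √0.36 = 0.6, so slope SDs of 0.8 and 1.2 are 1.3 and 2 times that, which is sizeable. AR(1) is also an assumption, since the article says only that residuals are correlated.
- **That the absence of a small-sample correction is an error.** Degrees-of-freedom methods are commonly left to the analysis plan, and this point does not rest on them.

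A reader may also say that a trend model would miss an immediate level shift. That is not established: session means and monthly estimates are planned as well. The 24-clinician simulations drop whole clinicians, whereas the planned model would keep their observed sessions, so those figures are approximate.

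Finally, the validity sentence can be read as the usual remark about dropout. It is nonetheless a statement about the models as described, and ignorable dropout does not secure standard errors when trend variation at the randomised level is left out.

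**Conclusion.** The point holds in conditional form. The written covariance model omits clinician-level slopes while a 12-week trajectory is modelled under clinician randomisation, and nothing elsewhere in the article supplies them. If clinicians' trends differ materially, inference on an arm-by-time contrast is anticonservative: about 7%, 12% and 19% rejection at slope SDs of 0.5, 0.8 and 1.2 components, against a nominal 5%. Every variance behind these figures is assumed. A second set of assumed variances shows the same pattern. The sentence on valid standard errors is overstated, and the Tele-BE effect is not tied to one contrast. This should be fixed before the trial data are analysed; it is not grounds to reject the design.

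**What to change.** 1. Write the arm and arm-by-time terms into the primary model.
2. Add a clinician random slope for time wherever arms are compared on trend. State a fallback if it does not converge: clinician-level slopes compared by t-test, or cluster-robust errors with a small-sample method.
3. Name the one contrast that serves as the Tele-BE effect. The Tele-BE minus Tele-AU difference averaged over weeks 1 to 12 is one suitable choice: it fits the Progression Criteria's interest in whether components are used more under Tele-BE, and it is insensitive to slope variation. Trend terms can then be descriptive.
4. Under Missing Data Considerations, make the validity statement conditional on a correct covariance model as well as on ignorable dropout.

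**Cost.** Wording only, with no change to data collection. Intervals for trend differences widen where slopes vary: in the simulation with 30 clinicians the mean SE rises from 0.373 to 0.499 at slope SD 1.0, but only from 0.349 to 0.364 when slopes do not vary. Convergence may be difficult with 24 to 30 clinicians, hence the fallback.
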